### Participants

#### Study population and sample size

We will recruit CTTH sufferers who meet the diagnostic criteria in the International Classification of Headache Disorders, 3rd Edition (ICHD-3) formulated by the International Headache Society [1]. According to a previous study [11], the proportion of responders (at least 50% reduction in days with headache) was 46% after acupuncture treatment versus 35% after superficial acupuncture (odds ratio, 1.32). In this study, we expect an odds ratio of 1.35 when acupuncture is compared with superficial acupuncture. Assuming a significance level of 0.05, a study power of 0.8, and a correlation of 0.5 between independent variables (including study groups, assessment intervals, and the number of headache days at baseline), 199 participants are required to reject the hypothesis that acupuncture is equivalent to superficial acupuncture. Taking a 10% attrition bias into consideration, we will recruit 218 participants in total, with 109 in each group.

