#### Primary outcome

The primary outcome measurement is the proportion of responders at week 16. A responder is defined as a participant with a decrease of at least 50% less headache days during 4 weeks. A participant with a reduction of less than 50% headache days, including anyone with missing data, is defined as a nonresponder. This outcome measurement will be assessed at week 16 after randomization.

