### Statistical analysis

Primary analysis will be based on intention-to-treat population, including participants with at least one assessment of the primary outcome and one acupuncture session. Per protocol (PP) analysis will be performed to test the robustness of the primary analysis. PP population will include participants receiving at least 12 sessions of acupuncture and be assessed at week 8 and 16.

The primary outcome will be analyzed with a random intercept logistic regression model, taking treatment allocation as a random factor and taking sex, age, and duration of headache as fixed factors. The secondary outcomes (headache days, headache intensity, SF-36, HAMA, HAMD results) will be analyzed using a generalized least squares regression model, with the same covariates as the primary outcome. For the rest of outcomes, we will make pairwise comparisons using a general linear model adjusted for baseline value, age, sex, and disease course. Missing values of the primary outcome will be imputed by the last-observation-carried-forward method. We will run several sensitivity analysis to ensure the robustness of the imputation: first, lost-to-follow-up participants in the acupuncture group will be recognized as nonresponders, whereas those in the superficial acupuncture group will be recognized as responders; second, lost-to-follow-up participants will be counted as responders in the acupuncture group but nonresponders in the superficial group; Third, all lost-to-follow-up participants will be treated as nonresponders. Missing values in the secondary outcomes will be imputed by using the multiple imputation method (*n* = 5).

All confidence intervals will be two-sided 95% intervals comparing acupuncture to superficial acupuncture and all statistical hypotheses will be two-sided tests. Analyses will be performed using the R and Stata programs.

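### The 10% attrition top-up treats lost participants as leaving the analysis, while the outcome definition and the analysis section each prescribe something else, so the power of 218 rests on no settled missing-data rule

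*Protocol article*

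**What the plan says.** All references are to the protocol article.

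- **Study population and sample size.** The error rate and power are given as "Assuming a significance level of 0.05, a study power of 0.8, and a correlation of 0.5 between independent variables". The base figure is "199 participants are required to reject the hypothesis that acupuncture is equivalent to superficial acupuncture", followed by the top-up: "Taking a 10% attrition bias into consideration, we will recruit 218 participants in total, with 109 in each group". The section cites responder rates of 46% and 35% from a previous study and then says "we expect an odds ratio of 1.35 when acupuncture is compared with superficial acupuncture".
- **Primary outcome.** The endpoint is responder status at week 16. Someone short of a 50% reduction, "including anyone with missing data, is defined as a nonresponder".
- **Statistical analysis.** The primary population needs at least one assessment of the primary outcome and one session. Missing primary-outcome values are filled by last observation carried forward (LOCF). Only the third sensitivity analysis says that "all lost-to-follow-up participants will be treated as nonresponders". On sidedness, "all statistical hypotheses will be two-sided tests".

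**The concern.** Adding a percentage for attrition replaces participants who contribute nothing to the analysis. It does not repair a smaller effect. If lost participants stay in the denominator as nonresponders, 10% loss multiplies both response rates, and hence the difference between arms, by 0.90. A 10% top-up does not make up for that.

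The sample-size section therefore assumes one fate for lost participants, the outcome definition gives them a second, and the analysis section a third. The stated power of 0.8 matches the first only. The issue would also survive a correction of the base figure: whoever recalculates 199 and again adds 10% would carry the same mismatch forward.

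**Working it through.** **Inputs.** Two-sided 5% test, 80% power, 199 needed, 218 recruited (109 per arm), 10% loss, 46% v 35%, odds ratio 1.35: all from the protocol. Assumed here: equal loss in both arms, planning rates that describe participants with data, and a simple two-proportion comparison at week 16.

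**The plan's own figures.** The top-up reproduces: 199 × 1.10 = 218.9, printed as 218. Dividing instead gives 199 / 0.90 = 221.1, so 222. The base of 199 does not reproduce as a two-sided week-16 comparison (pooled variance): 46% v 35% needs 624 in total. An odds ratio of 1.35 from 35% (odds 0.538 × 1.35 = 0.727, a rate of 42.1%) needs 1,476.

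**Formula.** Power = Φ(|pA − pC| / SE − 1.96), with SE = √{[pA(1 − pA) + pC(1 − pC)] / n} and n per arm.

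**Step 1: grant that 199 gives 80%.** With pC = 0.35 and n = 99.5, solve for pA. The result is 0.5437: difference 0.1937, SE 0.0691, ratio 2.802, and Φ(0.842) = 0.80. This is an odds ratio of about 2.2. It is a device for isolating the top-up and is not an effect stated in the protocol.

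**Step 2: apply each missing-data rule at 218 randomised, 10% lost per arm.**

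| Treatment of lost participants | Rates | n per arm | Difference | SE | Power |
|---|---|---|---|---|---|
| No loss | 54.4% v 35.0% | 109 | 0.1937 | 0.0661 | 83.5% |
| Excluded | 54.4% v 35.0% | 98.1 | 0.1937 | 0.0696 | 79.4% |
| Nonresponders | 48.9% v 31.5% | 109 | 0.1743 | 0.0654 | 76.0% |
| LOCF, responding at half the completer rate | 51.7% v 33.3% | 109 | 0.1840 | 0.0658 | about 80% |

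Under LOCF each arm's rate is p × (0.90 + 0.10f), where f is the lost participants' carried-forward response rate relative to completers. With f the same in both arms, power runs from 76.0% (f = 0) to 83.5% (f = 1).

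**Step 3: sensitivity.** Repeating steps 1 and 2 under nonresponder scoring gives 78% at a control rate of 20%, 77% at 25%, 74% at 45% and 73% at 50%. Pooled variance moves the 35% case only to 76.1%. Using 222 in place of 218 gives about 77%, so the shortfall is not a matter of rounding. At a 35% control rate, keeping 80% would take about 241 participants, a factor of 241 / 199 = 1.21.

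**Step 4: the protocol's own rates at 109 per arm.**

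- 46% v 35%, no loss: 0.11 / 0.0661 = 1.665, and Φ(−0.295) = 38%.
- 46% v 35%, lost excluded (98.1 per arm): 35%.
- 46% v 35%, nonresponder scoring (41.4% v 31.5%): 0.099 / 0.0648 = 1.527, and Φ(−0.433) = 33%.
- Odds ratio 1.35 from 35%: 19% with no loss, 17% under nonresponder scoring.

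**The case against.** A reader might infer that the endpoint simply keeps lost participants as nonresponders, so that 218 is shown to miss its 80%. The document does not support that. The analysis section names LOCF for the primary outcome and places all-nonresponder scoring third among the sensitivity analyses, which tells against its being the primary rule. Under LOCF, power may fall below or above 80%. The analysis population, read literally with a single week-16 endpoint, removes those lost earlier, and the top-up is then coherent at 79.4%. This objection stands and limits the point. It does not remove it: the literal population reading leaves both the nonresponder rule and LOCF with almost nobody to act on, and the sample-size section does not state the assumption about lost participants that LOCF would need to reach 80%.

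The 0.90 factor also presumes that the planning rates are completer rates. The protocol does not say how the cited study handled missing data. If 46% and 35% already count missing as nonresponse, no further dilution applies, though a top-up for attrition would then have no purpose under nonresponder scoring.

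Finally, the two-proportion test may not be the sponsor's method, since the text mentions a correlation of 0.5 and assessment intervals. A repeated-measures calculation for 46% v 35% with 7 or 8 assessments, correlation 0.5 and baseline adjustment comes to about 195 to 201. The text does not describe that calculation, and it does not use the odds ratio of 1.35 or a week-16 comparison alone.

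**Conclusion.** The point holds conditionally. The three sections do not agree on what happens to lost participants, and the top-up fits only their exclusion. If the outcome definition governs, the step from 199 to 218 does not restore power: about 76% in place of 80% at a 35% control rate, and 73% to 78% over control rates of 50% to 20%. Under LOCF it is about 76% to 83.5%; under exclusion, about 79%.

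These figures assume that 199 gives exactly 80%, that 10% is lost in each arm, and that the planning rates exclude missing data. Equal loss matters. Under nonresponder scoring at the back-solved rates (pooled variance), 15% loss with acupuncture and 5% in the control arm gives about 51%; the reverse gives about 92%.

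It would be tempting to read 76% as the trial's power. It is not, because it rests on an odds ratio of about 2.2 where the protocol plans for 1.35. The shortfall of about 4 points is also small beside the fact that 199 is not reproduced from the stated inputs. Nor is this a slip of multiplication: 199 × 1.10 is close to 218.

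**What to change.** 1. State in one place which rule governs the primary analysis, the nonresponder rule in the Primary outcome section or LOCF with its population in the Statistical analysis section, and align the other section with it.
2. In the sample-size section, restate the power of all 218 randomised under that rule. Start from response rates the protocol supports, and say whether those rates already count missing as nonresponse.
3. If they do not, and nonresponder scoring governs, multiply each arm's rate by 0.90. For 46% v 35% this gives about 33%, against 38% with no loss. If LOCF governs, state the response rate assumed for lost participants.
4. Do not print 76% as the trial's power unless the base of 199 has first been justified.

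The cost is a few sentences and one recalculation. No extra patients are asked for. The downside is a less favourable stated power.

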#### Inclusion criteria

Eligible participants should conform to ICHD-3 diagnostic criteria of CTTH and those who meet the following inclusion criteria will be included: (1) aged 18–65 years; (2) having TTH for more than 1 year; (3) suffering from TTH for at least 15 days per month on average during the previous 3 month; (4) able to complete the headache diary; (5) agree to participate in this study and provide written informed consent.

#### Exclusion criteria

Participants meeting any of the following criteria will be excluded: (1) headache is caused by other medical disorders (e.g., subarachnoid hemorrhage, cerebral hemorrhage, cerebral embolism, cerebral thrombosis, vascular malformation, arthritis, hypertension, or arteriosclerosis); (2) have taken prophylactic headache medication during the previous 3 months; (3) suffering from neurological diseases, mental disorders, immunodeficiency, bleeding disorders, or allergies; (4) having any serious disease of the heart, liver, kidney, or other organs; (5) those who are pregnant or lactating, or plan to be pregnant in the next 36 weeks; (6) unwilling to take part in the study or with low compliance, defined as the people who just plan to receive up to ten sessions of a total of 20 treatment sessions; (7) addicted to smoking, alcohol, or drugs; (8) involved in other clinical studies at the same time.

#### Dropout criteria

Participants will be removed if they are unwilling to continue this study, or fail to continue for at least 12 sessions of treatment.

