## Method and design

### Study design

This study is a parallel-design, patient-assessor blind RCT comparing an acupuncture treatment group with a superficial acupuncture control group. Two hundred and eighteen patients with CTTH will be recruited through but not limited to: reviewing and screening of outpatients in the Teaching Hospital of Chengdu University of Traditional Chinese Medicine, university media releases, community advertisement including distributing leaflets via regular community health counselling, media campaigns, and network recruitment.

Eligible participants will be randomly assigned to the acupuncture treatment group or the superficial acupuncture control group with a 1:1 ratio. The total observation period will be 36 weeks, including a 4-week baseline period, an 8-week treatment period and a 24-week follow-up period. They will receive 20 sessions of acupuncture or superficial acupuncture treatment over 8 weeks (three sessions per week in the first 4 weeks and two sessions per week in the following 4 weeks). During the baseline, treatment and follow-up periods, participants will not be allowed to take any prophylactic medications (e.g., amitriptyline, clomipramine, and mirtazapine) for CTTH, but will be permitted to use necessary analgesics (e.g., ibuprofen, paracetamol and ibuprofen) when headache is unbearable The type, dose and time of administration will be recorded in headache diaries. Assessments will be conducted at baseline and at 4, 8, 12, 16, 20, 24, 28, 32, and 36 weeks after randomization. Figures 1 and 2 illustrate the time schedule of enrolment, interventions, assessments, and visits of participants. The reporting of this trial is conducted according to the Standard Protocol Items: Recommendations for Intervention Trials (SPIRIT) guidelines (Additional file 1).

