#### Secondary outcome

The secondary outcome measurements are (1) number of headache days per 4 weeks, (2) the mean intensity of headache recorded by visual analogue scale score and grade of headache intensity per 4 weeks, (3) the reduction of medication intake per 4 weeks, (4) the 36-item short form health survey (SF-36) [20], (5) Hamilton Depression Scale (HAMD) [21] and Hamilton Anxiety Scale (HAMA) [22] results, (6) number of participants with adverse events (AEs) and serious adverse events (SAEs), (7) expectation values of acupuncture treatment, (8) the intensity of the *deqi* sensation.

All participants will be asked to complete a daily headache dairy and return them to assessors by emails, short messages or telephone calls throughout the whole 36-week observation period. The first three secondary outcomes will be extracted from the headache diaries. And the three outcomes followed will be assessed at each visiting time point. All of the above outcome measurements will be assessed at baseline, and at 4, 8, 12, 16, 20, 24, 28, and 32 weeks after randomization. Moreover, the expectation value of acupuncture treatment will be collected at baseline and week 8 after randomization, and the intensity of the *deqi* sensation will be assessed at 5 minutes after each treatment using the Massachusetts General Hospital Acupuncture Sensation Scale (MASS).

Details of AEs and SAEs will be documented during the 36-week period, such as occurrence time, duration, coping methods, and the correlation with treatment. AEs include bleeding, hematoma, fainting, severe pain, local infection, and so on, while SAEs are defined as life-threatening events, leading to significant or persisted disability, resulting in or prolonging hospitalization.

Researchers responsible for recruiting participants and assessors responsible for collecting data must receive training to ensure all of them have the same standards and understand the purpose, contents, and quality control of the trial. Detailed time points of outcome assessments are provided in Fig. 2.

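### The dropout rule does not separate stopping treatment from leaving the study; if removal ends follow-up, participants under 12 sessions have no week-16 outcome and the ITT set moves toward the per-protocol set or relies on imputation

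*Protocol article*

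**What the plan says.** Four parts of the protocol article bear on this.

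- **Dropout criteria:** "Participants will be removed if they are unwilling to continue this study, or fail to continue for at least 12 sessions of treatment". Nothing is said about data collection after removal.
- **Secondary outcome:** "All participants will be asked to complete a daily headache dairy and return them to assessors" by email, message or telephone, "throughout the whole 36-week observation period". No exception is made for removed participants.
- **Statistical analysis:** the ITT set comprises "participants with at least one assessment of the primary outcome and one acupuncture session". For the robustness check, "PP population will include participants receiving at least 12 sessions of acupuncture and be assessed at week 8 and 16".
- **Primary outcome:** responder status, of which the article says "This outcome measurement will be assessed at week 16 after randomization". Missing data count as nonresponse here. The Statistical analysis section instead names last observation carried forward (LOCF), with three sensitivity analyses for participants lost to follow-up: worst case, best case and all nonresponders.

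**The concern.** Attending too few sessions is a departure from treatment. Leaving the study is the end of observation. The dropout rule joins the two. Its session threshold is also the one that defines the per-protocol set, so a criterion that belongs to a secondary analysis appears to decide who stays in the trial.

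If removal means the end of follow-up, which is the natural reading under that heading, the plan creates missing primary outcomes by rule, and the missingness is tied to adherence. The arms differ in needle depth, manipulation and *deqi*, so the reasons for stopping, and how often it happens, may differ by arm. At stake are the validity of the primary comparison for the people removed and the value of the per-protocol analysis as a check on it.

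**Working it through.** **Timing.** Study design gives the schedule as "three sessions per week in the first 4 weeks and two sessions per week in the following 4 weeks". That is 3 × 4 = 12 sessions by week 4 and 12 + 2 × 4 = 20 by week 8. On this schedule, failure to reach 12 sessions is known by week 8 at the latest, at least 16 − 8 = 8 weeks before the primary endpoint. If removal ends follow-up, no removed participant has a week-16 value.

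**Effect on the analysis sets.** Take a participant with 1 to 11 sessions whose follow-up has ended.

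1. If the assessment condition of the ITT definition is enforced at week 16, this person is excluded. Everyone left has at least 12 sessions, and the ITT and per-protocol sets differ only on attendance at assessments.
2. If the person is kept, the outcome is imputed, as nonresponse or by LOCF.

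In neither case does the comparison of ITT with per-protocol use observed outcomes from people who stopped early.

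**Attrition figure.** The article plans 199 participants, 10% attrition and 218 in total: 199 × 1.10 = 218.9, printed as 218. Ten per cent of 109 is about 11 per arm. This is attrition from all causes. The share due to the session rule is not given, so the removal shares below are assumptions.

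**Direction of bias (illustration).** Let dA and dC be the shares removed in the acupuncture and control arms. Let pA = 0.46 and pC = 0.35 be the response rates among those retained (the article's planning rates), and let q be the response rate among those removed, assumed equal in both arms at 0.20 to 0.35.

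- All randomised: [(1 − dA)pA + dA·q] − [(1 − dC)pC + dC·q]
- Nonresponder rule: (1 − dA)pA − (1 − dC)pC
- Error of the nonresponder rule: q(dC − dA)

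For 5% v 15%:

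- Nonresponder rule: 0.437 − 0.2975 = 0.1395
- All randomised, q = 0.20: 0.447 − 0.3275 = 0.1195
- All randomised, q = 0.35: 0.4545 − 0.35 = 0.1045

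For 15% v 5%:

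- Nonresponder rule: 0.391 − 0.3325 = 0.0585
- All randomised, q = 0.20: 0.421 − 0.3425 = 0.0785
- All randomised, q = 0.35: 0.4435 − 0.35 = 0.0935

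| Removed, acupuncture v control | Nonresponder rule (points) | All randomised, q = 20% | All randomised, q = 35% | Error (points) |
|---|---|---|---|---|
| 5% v 15% | 13.95 | 11.95 | 10.45 | +2.0 to +3.5 |
| 15% v 5% | 5.85 | 7.85 | 9.35 | −2.0 to −3.5 |
| 10% v 10% | 9.9 | 9.9 | 9.9 | 0 |

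If removed participants are excluded instead, the analysis shows 46 − 35 = 11.0 points in every row. Against the all-randomised values the error is −0.95 to +0.55 in the first row, +3.15 to +1.65 in the second and +1.1 in the third. The direction again depends on the assumptions. A LOCF result cannot be computed, because the article gives no response rates at earlier visits.

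**Range under the plan's own extreme cases.** With r removed out of 109 in each arm, the retained difference in responders is 0.11 × (109 − r). At r = 11 this is 0.11 × 98 = 10.78.

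- All removed are nonresponders: 10.78 / 109 = 9.9 points
- Worst case: (10.78 − 11) / 109 = −0.2 points
- Best case: (10.78 + 11) / 109 = 20.0 points

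| Removed per arm | All nonresponders | Worst | Best |
|---|---|---|---|
| 5% (5) | 10.5 | 5.9 | 15.1 |
| 10% (11) | 9.9 | −0.2 | 20.0 |
| 15% (16) | 9.4 | −5.3 | 24.1 |
| 20% (22) | 8.8 | −11.4 | 29.0 |

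**The case against.** The strongest reply is that the article never says data collection stops. The Secondary outcome section asks all participants for diaries over the full period, and a condensed article may leave withdrawal procedures to a fuller document. A reader might infer that the week-16 data of removed participants are never collected. That goes beyond the text, so the point is conditional. What stands is that one section removes these people, another asks everyone for diaries and neither refers to the other, so site staff would have to guess.

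Three other strong readings are not supported either.

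- A reader might take the ITT set to need only one session. It also needs a primary-outcome assessment, and that second condition is what could exclude removed participants.
- A reader might conclude that an ITT analysis on real outcomes is impossible. Only the removed participants are affected. At an assumed 10%, about 98 of 109 per arm still have observed outcomes.
- A reader might expect the rule to favour acupuncture. That holds only for some imbalances. The sign reverses when the imbalance does.

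The plan also has safeguards. The extreme-case analyses would contain the truth: in the 5% v 15% illustration they span 0.437 − 0.4475 = −1.05 points to 0.487 − 0.2975 = 18.95 points, against 10.45 to 11.95. The Discussion adds retention contacts and an analysis of the characteristics of dropouts. The per-protocol set keeps its assessment conditions, so it need not coincide with the ITT set. These measures are worth having, but they bound or describe the lost information. They do not replace it, and the retention effort works against a rule that creates dropouts.

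**Conclusion.** The point holds in conditional form, with moderate confidence. The dropout rule does not distinguish stopping treatment from leaving the study, and it must be reconciled with the diary instruction and the two analysis-set definitions. If removal ends follow-up, participants under 12 sessions have no week-16 outcome, and the primary analysis either omits or imputes them.

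The size is not known from the documents. Under the assumptions shown, an imbalance of 10 percentage points in removal shifts the estimate by 2 to 3.5 points in either direction under the nonresponder rule. Equal removal with equal response among those removed gives no shift under that rule. At 10% removed per arm, the plan's extreme cases leave the 11-point planning difference anywhere between about −0.2 and 20 points. These figures rest on assumed removal shares, on 46% v 35% among those retained and, for the bias figures, on a common response rate of 20% to 35% among those removed.

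**What to change.** Amend the Dropout criteria section and align it with Secondary outcome and Statistical analysis:

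- State that fewer than 12 sessions is a per-protocol criterion only and does not end participation in follow-up.
- Keep participants who stop or miss sessions in the study, with diaries and assessments to week 32, unless they withdraw consent to data collection.
- Record stopping treatment and leaving follow-up as separate events, each with date and reason.
- Include these participants in the ITT analysis with their observed week-16 outcome. Keep the extreme-case analyses for outcomes that are still missing.

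This concerns data collection and analysis sets only, and says nothing about who should stop treatment. The cost is a short amendment and a few more contacts by email, message or telephone, which the protocol already uses. It will not recover participants who refuse all further contact.
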